## **2. RATIONALE**

We aim to improve outcomes of onco-geriatric patients' surgical management. Our research project will focus on quality of life and functional recovery after surgery. The most important expected result will be the collection of data that clinicians will be able to exploit in the management of frail and 'pre-frail' patients with the potential to reduce disparities in elderly patient care. In addition, the 'multidisciplinary work ethic' in the management of this specific group of patients, regardless for their primary condition, will be extensively promoted to determine small but clinically important incremental improvements in elderly care.

We need to conduct the GO SAFE study for several reasons:

- There is a dramatic lack of knowledge on elderly cancer surgical patients
- Although survival is commonly reported after surgery, quality of life (QoL) and functional recovery (FR), including nutritional status, are rarely measured
- To promote the practice of a multidisciplinary management of elderly cancer patients
- To understand how frailty, comorbidities and malnourishment are associated with early and long-term clinical outcomes after surgery in elderly cancer patients
- To obtain prospective data to assist clinicians in tailoring the care, avoiding under/over-treatment
- To identify new strategies to improve functional outcomes (as cardiorespiratory/nutritional prehabilitation)

To identify areas warranting further research studies and surgical audit in the older adults cancer population

## **3. AIM OF THE STUDY**

GO SAFE study is a prospective international collaborative high-quality registry aiming to gain knowledge about postoperative outcomes in older cancer patients with a particular emphasis on QoL and FR. The target is to obtain meaningful data to assist clinicians in tailoring the care,

avoiding under/over-treatment, providing robust data to identify new strategies to improve functional outcomes in older cancer patients.

### **3.1 Primary Objective**

To evaluate the effects of surgery on patients' life perception by comparing pre- and post-operative QoL in elderly patients undergoing major surgery for solid malignancies using a self-reported Quality of Life assessment tool (EQ 5D-3L)

### **3.2 Secondary Objectives**

- To evaluate FR in terms of nutritional status, restoration of daily activities (ADL) and cognitive status (Mini-Cog)
- To evaluate 3 and 6 months postoperative morbidity and mortality
- To obtain prognostic factors for postoperative functional recovery which will assist in the treatment planning /intervention of future elderly patients who are offered surgery for cancer
- To identify variables affecting postoperative quality of life

## **4. STUDY PROTOCOL**

### **4.1 Centres and Investigators**

We aim to involve in the study as many centers as possible. All surgical units performing cancer surgery in elderly patients are invited to participate. Participating investigators will be surgical oncologists. Each center will require approval from local Institutional Review Board and/or the Ethic Committee before starting to enroll patients.

Investigators will be responsible to obtain a written informed consent from each eligible patient in according to the local IRB regulation, ahead of surgery (please see note below in case of demented patients). Every center shall commit to send clinical data after the 6-month follow up.

Periodic evaluation of patient data entry, centers' activity, and cohesion of the centers will be shared among the investigators.

#### **4.2 Study Design**

GO SAFE is a multicenter international observational prospective cohort study. The study is non-for-profit. Recruiting centers will collect data prospectively. Recruited patients will be followed for 6 months after their surgery. The original treatment plan, as designed by each individual recruiting centre, will not be altered or affected by the study inclusion.

#### **4.3 Study Population**

Centers should ensure that they would make every possible effort to include all consecutive eligible patients during the study period and provide completeness of data entry to ensure a 'real-life' study.

##### **4.3.1 Inclusion Criteria**

1. All consecutive patients, both gender, aged  $\geq 70$
2. Patients affected by solid malignancy
3. Patients undergoing elective major surgical procedures with curative or palliative intent (all major procedures including any resection, for any cancer, via any operative approach, open, laparoscopic, robotic, etc...)
4. Informed consent obtainment

##### **4.3.2 Exclusion criteria**

1. Patients undergoing emergent/urgent surgical procedures
2. Planned hospital stay less than 48 hours

#### **4.4 Local approvals**

Inclusion in the study does not imply any deviation from the current standard of practice, and no change is expected to the perioperative treatment at any point. Patients will be only asked to complete simple screening/assessment tests: for this reason this study should be registered as a prospective observational study at each participating hospital IRB. It is the responsibility of the local team to ensure that regulatory process is completed for its hospital. Participating centres will be asked to confirm that they have gained formal approval and to provide an Identification Number.

### **5. PROCEDURES AND DATA COLLECTION**

#### **5.1 Informed Consent**

It is the responsibility of the investigator, or a person designated by the investigator, to obtain (if applicable) written informed consent from each individual participating in this study. When applicable, each patient/health care proxy must sign and date the latest approved version of the Informed Consent form before any study specific procedures are performed.

Patients must receive an explanation that they are completely free to refuse to enter in this study and to withdraw from it at any time and for any reason without prejudice to future care, and with no obligation to give the reason for withdrawal. The original signed form will be retained at the study site. A copy of the informed consent form will be delivered to the patient. A form for obtaining written informed consent for this observational study will be provided.

#### **5.2 Registration (CRF A)**

All patients for whom eligibility criteria have been verified will be registered by each participating center in the eCRF.

The following data will be collected at registration:

- Patient's Date of birth
- Patient's Gender
- Date of Informed consent
- Date of registration

- Center informations

### **5.3 Data Collection**

Clinical reporting forms (CRFs) have been designed to be completed along the normal daily-life practice, trying to minimize the ‘extra work’ for local investigators. Tests, carried out at baseline and follow-up evaluation, could be easily completed by surgical trainees, medical students and nurses adequately trained. Surgical data analysis, including detection of postoperative complications, should require the supervision of an attending/consultant surgeon.

CRFs are to be completed through use of an EDC system. Sites will have access to a manual for appropriate CRF completion. All CRFs should be completed by designated, trained site staff. CRFs should be reviewed and electronically signed and dated by the investigator or a designee.

If a correction is required for an CRF, the EDC system will create an electronic audit trail.

Participants must maintain quality of their database and update their database. Access to the raw data will be according to agreement of both parties. Each center must keep a file of all consecutive patients that have been entered in the database for random quality monitoring.

#### **5.3.1 Baseline evaluation (CRF B)**

For every eligible patient, demographic data will be collected followed by a fast preoperative functional assessment including:

- Charlson Comorbidity Index
- “Timed Up and Go” test
- Nutritional Risk Screening (NRS)
- American Society of Anesthesiology (ASA) score
- ECOG Performance Status
- G8 geriatric screening tool
- Mini-Cog
- Activities of Daily Living (ADL)
- Quality of Life (EQ 5D-3L, Self or Proxy-1 version).

- History of delirium during illness or hospital admission
- History of Smoking
- History of falls in the 6 months prior to the operation
- Living situation
- Lab's (Albumin, Hemoglobin, Creatinin)
- Polipharmacotherapy (total number of medications)
- Preoperative chemotherapy/radiation therapy
- Involvement of geriatric specialist in preoperative care

### ***5.3.2 Operative details and early postoperative outcome (CRF C)***

Data regarding surgical procedures and perioperative measures will be collected. Complications will be reported and graded according to Clavien-Dindo Classification.

- Cancer site
- Surgical Procedure Category: Ortho, Gyn, Breast, Upper-GI, Colorectal, HBP, Peritoneum, Thoracic (esophagus), Head & Neck, Urology
- Type of procedure (describe)
- Type of anesthesia (General, Spinal, Epidural)
- Type of surgery (palliative, curative)
- Duration of anaesthesia (min)
- Surgical approach (Open/Laparoscopic/Robotic....)
- Need of ICU stay (Y/N; n. days)
- Perioperative blood transfusions (Units of Packed RBC's) within the surgical admission
- Postoperative length of stay (days in surgical unit)
- Patient discharged to same preoperative setting
- Patient transferred to Medicine/Rehabilitation facility
- Tumor stage (TNM/Stage)

- Involvement of geriatric specialist in postoperative care
- 30 day morbidity (Clavien-Dindo)
- 30 day mortality

### **5.3.3 Follow up (CRF 3M-6M)**

Three- and six-month follow up data will be collected after surgery within a range of 2 weeks from the due date.

| Data                                | 3 months | 6 months |
|--------------------------------------------|-----------------|-----------------|
| • Morbidity (Clavien-Dindo)                | X               | X               |
| • Mortality                                | X               | X               |
| • Living situation                         | X               | X               |
| • Weight                                   | X               | X               |
| • Nutritional Screenig                     | X               | X               |
| • “Timed Up and Go” test                   | X               | X               |
| • Mini-Cog                                 | X               | X               |
| • ECOG Performance Status                  | X               | X               |
| • ADL                                      | X               | X               |
| • Self-reported Quality of Life (EQ 5D-3L) | X               | X               |
| • Postoperative Chemotherapy               | X               | X               |
| • Postoperative Radiation Therapy          | X               | X               |
| • Rehabilitation program                   | X               | X               |
| • Nutritional supplement                   | X               | X               |

- Involvement of a geriatric specialist

X

X

Local investigators should be also proactive in identifying postoperative events. For example they may review patients notes during admission and before discharge, as well as they could review hospital and outpatient clinic systems to check for readmission and/or other unplanned events.

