# **6 STATISTICAL CONSIDERATIONS**

## **6.1 Data analysis**

The Full Analysis Set (FAS) consists of all registered patients.

The primary endpoint will be measured for all registered subjects who fulfill preoperative and postoperative EQ VAS. Demographic and baseline patient characteristics will be summarized for all patients in the FAS. Continuous-scaled variables (e.g., age) will be summarized with means, medians, standard deviations, quartiles, and minimum and maximum values. Categorical variables (e.g., sex) will be summarized using patient counts and percentages. Study endpoints and variables will be evaluated using descriptive statistics, and the key figures of the distributions will be presented in tables. Univariate analyses will allow for a first overview of potentially influential factors.

Multiple linear regression models will be performed in order to evaluate predictors of functional recovery at 3 months and 6 months after surgery.

Exploratory subgroup analyses will be performed. Missing values will be replaced and estimated using multiple imputations. Furthermore, sensitivity analysis will be executed using complete-case analysis.

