## **6.2 Sample size**

A sample size of 265 patients who completed pre and postoperative EQ VAS questionnaires will have a 90% power to detect an effect size of 0,2 between pre and post surgery ,using a paired t-test with a 0,05 two sided significance level.

Given a potential loss to follow-up (about 10%), uncompleted questionnaires (about 10%) and postoperative mortality (about 15%), the sample size will be increased to 350-400 patients (see

ref 18 and 19).

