## APPENDIX A: PROTOCOL CHANGES

### REASON FOR CHANGES

The protocol has been amended to include patients with moderate severe cognitive impairment into the primary endpoint evaluation, through the use of the proxy version of the EQ-5D-3L questionnaire. Moreover the procedure for Informed Consent obtainment has been better detailed.

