**Section 5.3.1. Baseline evaluation (CRF B) pag,13:**

**Original text**

[...]

- Self reported Quality of life (EQ-5D-3L). This test will not be administered to patients with moderate severe cognitive impairment (Mini Cog <3)

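### The amendment admits proxy EQ-5D-3L ratings at baseline only; the 3- and 6-month schedule and the primary objective still say self-reported

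*Protocol*

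**What the plan says.** The reason given for the amendment in Appendix A is to "include patients with moderate severe cognitive impairment into the primary endpoint evaluation, through the use of the proxy version of the EQ-5D-3L questionnaire". Appendix A lists changes to two sections: 5.1 (a health care proxy may sign the consent form) and 5.3.1 (the baseline list).

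The current text reads as follows:

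- Section 5.3.1, baseline: "Quality of Life (EQ 5D-3L, Self or Proxy-1 version".
- Section 5.3.3, 3 and 6 months: "Self-reported Quality of Life (EQ 5D-3L".
- Section 3.1, primary objective: pre- and postoperative quality of life are compared "using a self-reported Quality of Life assessment tool (EQ 5D-3L".
- Section 6.1: "The primary endpoint will be measured for all registered subjects who fulfill preoperative and postoperative EQ VAS".
- Section 6.2: "A sample size of 265 patients who completed pre and postoperative EQ VAS questionnaires will have a 90% power" for a standardised effect of 0.2, by a two-sided paired t-test at 0.05.

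No section allows a proxy at follow-up, asks for the same respondent at each visit, or lists the respondent as a data item.

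**The concern.** The primary endpoint is a change within the patient, so a proxy rating at baseline brings nobody into it unless there is also a usable rating after surgery. Sections 5.3.3 and 3.1 allow only self-report there. This leaves two literal readings for a patient with a proxy baseline:

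- **No permitted follow-up value.** The patient stays in the study but has no complete pair, and the amendment misses its purpose.
- **Self-report at follow-up.** The difference then contains a change of rater as well as any change in health. Section 4.2 describes a cohort without a control group, so the paired test cannot tell a rater effect from an effect of surgery.

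Both outcomes fall on the cognitively impaired patients for whom the amendment was written. Sites that read the text differently would also produce different kinds of pairs.

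**Working it through.** **1. The passages side by side.**

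| Place in protocol | Proxy allowed? |
|---|---|
| Appendix A, stated purpose | Yes, for the primary endpoint |
| 5.3.1, baseline | Yes (self or Proxy-1) |
| 5.3.3, 3 and 6 months | Not named; self-reported |
| 3.1, primary objective | Not named; self-reported |
| 6.1, primary endpoint | Silent on respondent; needs a value before and after surgery |

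The inconsistency lies within the current text. It does not depend on comparing that text with superseded wording.

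**2. The plan's own figure.** For a paired t-test with standardised effect 0.2, two-sided alpha 0.05 and power 0.90, the noncentral t distribution gives a smallest n of 265 (power 0.9004). The normal approximation is ((1.960 + 1.282)/0.2)² ≈ 263. The stated 265 reproduces and is not in dispute.

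**3. If respondents switch.** Let p be the share of pairs that go from proxy to self, and b the systematic proxy-self gap in SDs of the change score, the unit in which 0.2 is expressed. Then:

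- shift in mean change = p × b
- SD of the change is inflated to √(1 + p(1 − p)b²)

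Neither p nor b is in the documents. The values below are assumptions, evaluated with 265 pairs. The type I error column assumes no true change. The power column assumes a true effect of 0.2 with the gap running against it.

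| p | b | Shift p × b | Shift / 0.2 | Type I error | Power |
|---|---|---|---|---|---|
| 5% | 0.2 | 0.01 | 5% | 0.053 | 0.87 |
| 10% | 0.3 | 0.03 | 15% | 0.077 | 0.78 |
| 20% | 0.3 | 0.06 | 30% | 0.16 | 0.62 |
| 20% | 0.5 | 0.10 | 50% | 0.36 | 0.36 |
| 30% | 0.5 | 0.15 | 75% | 0.66 | 0.12 |

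**4. If these patients have no follow-up value.** The planned losses in section 6.2, taken as independent, leave 0.9 × 0.9 × 0.85 = 0.6885 of those enrolled: about 241 of 350 or 275 of 400. An assumed further loss of 5-30% leaves 228 to 168 pairs from 350 (power 0.85 to 0.73), or 261 to 192 from 400 (power 0.90 to 0.79). Part of this loss may already sit in the 10% allowed for uncompleted questionnaires.

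**The case against.** The strongest reply is that self-reported in 5.3.3 and 3.1 is leftover wording. The stated purpose, combined with an endpoint that needs both measurements, implies proxy use at follow-up too, and sites may have done just that with the CRF completion manual and trained staff mentioned in section 5.3. This is plausible, and it means that mixed pairs and lost patients are risks of the text and not established facts. It does not remove the contradiction, because nothing in the protocol says so and sites could differ.

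It can also be said that missing pairs need not threaten power. Section 6.1 plans multiple imputation with a complete-case sensitivity analysis. Supplementary Table 3 totals 942 procedures, and in Supplementary Table 4 the 494 patients at 52.4% imply 494/0.524 ≈ 943 patients. Even 942 × 0.6885 × 0.80 ≈ 519 pairs is well above 265. This stands as to power. Whether impaired patients are represented remains open, and their missingness would be tied to cognitive status. Neither imputation nor a larger sample removes a bias from changing respondents.

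A reader might infer that the amendment deleted the only cognitive cut-off and left sites free to choose the version. The documents do not support this. The deleted sentence read "This test will not be administered to patients with moderate severe cognitive impairment (Mini Cog <3"; it barred the questionnaire altogether and was not a rule for choosing a version. Supplementary Table 2 still gives a Mini-Cog threshold of 2 or below on a 0-5 scale, which is the same cut.

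The handling of proxy ratings could be in an SAP that was not available for this review. An SAP cannot, however, supply a rating that was not collected or a respondent type that was not recorded.

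**Conclusion.** The point holds as an incomplete amendment. Baseline admits a proxy, follow-up and the primary objective do not, and the endpoint needs both ends of the pair. Following the text literally either loses these patients from the primary endpoint or confounds respondent with time.

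The size cannot be settled from the documents. The assumed ranges give a shift of 0.01 to 0.15 SD of the change score against a design effect of 0.2, so the effect may be negligible or material, and its direction is unknown. The switching share is at most the share with a proxy baseline, since a switcher must need a proxy before surgery and then self-report after it. With few such patients the effect is small.

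A reader might infer from the table that the primary result is biased by some definite fraction of the design effect. That does not follow, because every row rests on assumed inputs. Severity: should-fix.

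**What to change.** - **Section 5.3.3:** replace "Self-reported Quality of Life (EQ 5D-3L" by the baseline wording, "Quality of Life (EQ 5D-3L, Self or Proxy-1 version", with the addition: same version as at baseline wherever possible.
- **Section 3.1:** delete self-reported.
- **eCRF:** record the respondent type (self or proxy) at baseline, 3 months and 6 months. For data already collected, classify pairs by respondent where this can be recovered.
- **Analysis:** keep all pairs in the primary analysis. Add two sensitivity analyses, one restricted to pairs with the same respondent and one to self-self pairs.

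The primary analysis should not itself be restricted to same-respondent pairs. That would select on an event after surgery: patients who begin to need a proxy because their cognition declines would leave the main result, although cognitive status is one of the recovery outcomes in section 3.2. The words wherever possible serve the same end, since a patient who can no longer self-report should still have a value.

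The cost is a wording amendment in two sections, one eCRF field per visit and a little more analysis. A respondent effect, if there is one, stays in the primary estimate, but the sensitivity analyses would show whether it matters.

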#### 5.4 Study plan flowsheet and CRF completion times

|                                                            |        |
|------------------------------------------------------------|--------|
| REGISTRATION                                               | CRF A  |
| PREOPERATIVE ASSESSMENT
(BASELINE EVALUATION)           | CRF B  |
| ↓                                                          |        |
| OPERATIVE DETAILS
EARLY POSTOPERATIVE OUTCOME (1 month) | CRF C  |
| ↓                                                          |        |
| FOLLOW UP
3 months                                      | CRF 3M |
| 6 months                                                   | CRF 6M |

#### 5.5 Confidentiality

Personal patients' data will not be shared to anyone outside of the research team. The information collected in this research project will be kept private. All patient information will be anonymized. The database used is certified, highly secured and is stored in a encrypted server that meets all the requirements for data-safety and privacy set by international law.

## **5.6 Data quality assurance**

- Medical review with investigators
- CRF quality check, query firing, data cleaning
- Early feedback with local research team via teleconferences

# **6 STATISTICAL CONSIDERATIONS**

## **6.1 Data analysis**

The Full Analysis Set (FAS) consists of all registered patients.

The primary endpoint will be measured for all registered subjects who fulfill preoperative and postoperative EQ VAS. Demographic and baseline patient characteristics will be summarized for all patients in the FAS. Continuous-scaled variables (e.g., age) will be summarized with means, medians, standard deviations, quartiles, and minimum and maximum values. Categorical variables (e.g., sex) will be summarized using patient counts and percentages. Study endpoints and variables will be evaluated using descriptive statistics, and the key figures of the distributions will be presented in tables. Univariate analyses will allow for a first overview of potentially influential factors.

Multiple linear regression models will be performed in order to evaluate predictors of functional recovery at 3 months and 6 months after surgery.

Exploratory subgroup analyses will be performed. Missing values will be replaced and estimated using multiple imputations. Furthermore, sensitivity analysis will be executed using complete-case analysis.

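### Section 6.1 limits the primary EQ VAS comparison to completers but also plans imputation with a complete-case sensitivity analysis; on the reading section 6.2 supports, that check repeats the primary analysis

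*Protocol*

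**What the plan says.** Protocol section 6.1 contains four statements that bear on the primary endpoint.

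- The analysis set: "The Full Analysis Set (FAS) consists of all registered patients".
- The primary endpoint: "The primary endpoint will be measured for all registered subjects who fulfill preoperative and postoperative EQ VAS".
- Missing data: "Missing values will be replaced and estimated using multiple imputations".
- The check: "Furthermore, sensitivity analysis will be executed using complete-case analysis".

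The imputation sentence names no endpoint. It comes after the regression models for functional recovery and shares a paragraph with the exploratory subgroup analyses.

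Section 6.2 bases the sample size on completers: "A sample size of 265 patients who completed pre and postoperative EQ VAS questionnaires will have a 90% power". The target is a standardised pre-post difference of 0.2, assessed by a paired t-test at the two-sided 5% level. It then raises enrolment to 350-400 to allow for about 10% loss to follow-up, about 10% uncompleted questionnaires and about 15% postoperative mortality.

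This is current text. Appendix A changes only sections 5.1 and 5.3.1.

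**The concern.** Requiring both EQ VAS values defines a complete-case analysis. Imputing missing values and calling complete-case the sensitivity analysis describes a different plan. Both cannot govern EQ VAS, and section 6.1 does not say which one does. An analyst could follow either and claim to have kept to the protocol, and the choice could be made after the data are seen.

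The completer rule also selects patients. It drops those who are alive but did not return or did not fill in the form. In patients aged 70 or over after major cancer surgery, that is unlikely to be unrelated to quality of life. If the planned sensitivity analysis uses the same patients and the same values, it cannot show whether selection has moved the result.

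**Working it through.** **Inputs from section 6.2:** 265 completers, 90% power, effect size 0.2, paired t-test, two-sided 0.05; losses of about 10%, 10% and 15%; enrolment 350-400. **Assumed, not in the protocol:** that patients lost to follow-up are alive, and that the change in patients alive without a pair is worse than in completers by 0.3 to 0.5 SD.

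**1. The plan's own figure.** Exact paired t-test power (noncentral t) gives n = 265 with power 0.9004. The normal approximation, ((1.960 + 1.282)/0.2)², gives 263. The stated 265 reproduces.

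**2. What the sensitivity analysis adds on the completer reading.** Every patient in the set has both values, so there are no missing EQ VAS pairs to impute. The complete-case set is the same set, and the difference between the two analyses is exactly 0.

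**3. Which reading section 6.2 supports.** It powers the study on completers and makes up for losses by enrolling more patients. That fits a completer-based primary analysis rather than imputation over all registered patients.

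**4. Registered patients with no pair.**

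- Rates added: 10 + 10 + 15 = 35%, leaving 65% complete.
- Rates multiplied: 1 − 0.90 × 0.90 × 0.85 = 1 − 0.6885 = 31.15%, leaving about 69% complete.

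That is 228-241 completers of 350, or 260-275 of 400.

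**5. Alive but without a pair.**

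| | Rates added | Rates multiplied |
|---|---|---|
| Share of registered patients | 10 + 10 = 20% | 0.85 × (1 − 0.90 × 0.90) = 16.15% |
| Share of survivors | 20/85 = 0.235 | 16.15/85 = 0.19 |

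**6. Size of the bias among survivors.** Bias = (share of survivors without a pair) × (assumed gap).

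| Assumed gap | Rates added | Rates multiplied |
|---|---|---|
| 0.3 SD | 0.235 × 0.3 = 0.071 | 0.19 × 0.3 = 0.057 |
| 0.5 SD | 0.235 × 0.5 = 0.118 | 0.19 × 0.5 = 0.095 |

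The range is about 0.06 to 0.12 SD, or roughly 30% to 60% of the 0.2 SD design effect.

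**7. Does the sign of the change matter?** With rates added and completers at +0.20 SD, the survivor mean is (65 × 0.20 + 20 × (0.20 − 0.3))/85 = 0.129 for a 0.3 SD gap, and 0.082 for a 0.5 SD gap. With completers at −0.20 SD, it is −0.271 and −0.318. The shift is 0.071 or 0.118 SD either way. In the first case completers overstate a gain; in the second they understate a decline.

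**8. The other reading.** If imputation over the Full Analysis Set is primary, complete-case is a different analysis. An illustrative simulation assumed baseline mean 70 and SD 18, about 35% missing depending on baseline, and a true mean change of 0. Complete-case averaged −1.8 VAS points and imputation −0.02. In that set-up patients with low baseline scores were more often missing, and the completer mean came out too low. So the direction of bias depends on how values go missing; the direction in step 6 follows from the assumed gap.

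**The case against.** The strongest answer is that the text can be read without contradiction: paired completers for EQ VAS, and imputation for the regression and subgroup work beside which the sentence stands. That reading is fair, and section 6.2 supports it. But it is also the reading on which complete-case analysis adds nothing for the primary endpoint. It removes the conflict and leaves the selection problem with no check.

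Three stronger claims might be inferred, and the protocol does not support them.

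- **That imputation is the main method for the primary endpoint.** Section 6.1 never says so. It can only be inferred from the sensitivity label on complete-case.
- **That the primary result has no robustness check at all.** This holds only on the completer reading. With imputation over the Full Analysis Set as primary, complete-case is a limited check, though the text leaves open whether EQ VAS would be imputed after death.
- **That completers overstate the benefit by 1.5 to 2.4 times.** That ratio needs completers to improve by 0.20 SD, an assumed 0.3 to 0.5 SD gap, and rates that add. Section 6.2 gives 0.2 as a detectable effect under a two-sided test, with no direction. With rates multiplied the ratio falls to about 1.4 to 1.9, and with a decline it becomes an understatement of harm. Only the shift in SD units is stable.

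Two further points stand in part. Section 6.2 does not say that patients lost to follow-up are alive, or that uncompleted questionnaires are only postoperative. And section 5.3.1, as amended, allows a proxy EQ-5D-3L so that cognitively impaired patients enter the primary evaluation. This reduces selective loss, but incompletely, because the follow-up schedule in section 5.3.3 still lists the questionnaire as self-reported.

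Imputation predictors and missing-not-at-random analyses are matters for an SAP, and their absence here is not the complaint.

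**Conclusion.** The point holds in this form: section 6.1 states a completer-only rule for the primary endpoint and an imputation rule whose scope it leaves open. On the reading that section 6.2 supports, the named sensitivity analysis is identical to the primary analysis and cannot detect selective completion.

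The plan's rates imply that 31% to 35% of registered patients will have no pair, and 16% to 20% for reasons other than death if those lost to follow-up are alive. The bias of 0.06 to 0.12 SD among survivors rests on the assumed 0.3 to 0.5 SD gap, which no passage supplies. It is an indication of scale, not an estimate. This is more than missing detail, because the protocol states a rule that is open to selection bias and pairs it with a check that may check nothing. It should be settled before the data are analysed.

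**What to change.** Reword section 6.1 so that one set and one method are primary for EQ VAS.

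- **Primary:** mean EQ VAS change in Full Analysis Set patients not known to have died by the visit, estimated by multiple imputation or a repeated-measures mixed model. Use baseline and other-visit EQ VAS, ECOG, ADL, Timed Up and Go and complications (Clavien-Dindo). Impute nothing after death.
- **Sensitivity:** the paired t-test in patients with both values, labelled as the complete-case analysis.
- **Optional:** a missing-not-at-random check that shifts imputed values downward, for example by 0.3 to 0.5 SD.
- **Scope:** state whether the imputation sentence also covers the regression and subgroup analyses.

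Sections 5.3.1 to 5.3.3 already collect all of these variables, so no new data are needed. The 265 calculation is unaffected. The cost is rewording and a little more analysis. The price in assumptions is reliance on missing at random, and some patients lost to follow-up will have unknown vital status, which is why the set is worded as not known to have died.
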